### Reference standard

2.5

Metastatic disease will be deemed without further imaging or examinations if the presentation is considered of typical morphology and pattern for PCa, especially considering lymph nodes and bones. In other tissues, metastases will also be suspected by a typical appearance, and biopsy will be intended only as a part of the clinical set‐up when possible and clinically relevant. Biopsies are not performed solely as a part of the study. Further imaging will be used as reference standard to confirm or exclude metastatic disease when clinically indicated (see Table 3).

**TABLE 3 bco2243-tbl-0003:** Reference standard.

	Metastases deemed
Any organ but the prostate gland	Pathology confirming metastasis
Lymph nodes	Equal to or more than 8 mm, round and with no fat in the hilum, for PSMA‐PET with uptake of PSMA
Bones	Marked uptake of activity with or without malignant morphology in CT and not related to joint with degenerative changes or a fracture, or malignant morphology with uptake
Liver	Biopsy if possible and clinically relevant, for PSMA‐PET with uptake of PSMA
Lung nodules—malignant	Biopsy if possible (and clinically relevant)
Disseminated disease	If disseminated disease with a typical pattern for prostate cancer, disseminated disease can be determined without further imaging or biopsy
Metastases	Further imaging supporting the suspicion of a metastasis

Abbreviations: CT, computed tomography; PET, positron emission tomography; PSMA, prostate‐specific membrane antigen.

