### Study design

1.2

This trial is a randomised controlled clinical trial following the Consolidated Standards of Reporting Trials (CONSORT) guidelines.^12^ A total of 448 patients (power calculation is in the statistical section) will be included and randomised into a control group (A) and an intervention group (B) (Figure 1 and Appendix A). Patients in Group A will be staged by Na[^18^F]F‐PET/CT, that is, CECT for lymph node and soft tissue metastases, and Na[^18^F]F‐PET for bone metastases according to current practice at our centres. Patients in Group B will be staged by [^18^F]PSMA‐1007‐PET/CT (including CECT) for lymph node, bone and soft tissue metastases. A subgroup of patients in Group B will have a blinded Na[^18^F]F‐PET scan with low‐dose CT (ldCT) for attenuation correction for the purpose of performing comparative accuracy analyses.

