### Clinical management

2.6

The patients will be discussed in a multidisciplinary team (MDT) conference based on the results of the scans and staging performed accordingly. If in doubt of metastases, further imaging or biopsy will be performed if possible and relevant. The MDT will suggest a treatment strategy that follows the contemporary national guidelines.^15^ In a shared decision process with the patient, the final choice of treatment will be decided upon, and the patients may be treated by prostatectomy, radiotherapy, androgen deprivation therapy (ADT), chemotherapy or antiandrogens and, eventually, in combinations.

### 
QoL

2.7

QoL will be assessed using the following widely used questionnaires—all of them were translated and cross‐culturally validated in Danish:
Functional Assessment of Cancer Therapy‐Prostate (FACT‐P)—39 items^16^;European Quality of Life‐Five Dimensions (EQ‐5D‐5L) covering five dimensions: mobility, self‐care, usual activities, pain/discomfort and anxiety/depression—25 items and a VAS scale^17^, ^18^, ^19^; andThe Expanded Prostate Cancer Index Composite (EPIC‐26)—26 items.^20^
The patients will be asked to fill in the questionnaires electronically or on paper at fixed time points in their pathway (at diagnosis and after 3, 6, 12, 24, 60, 120 and 234 months after enrolling—enabling data collection for approximately 20 years after inclusion of the last patient). Time points of evaluation are chosen to be able to evaluate QoL over time after diagnosis and treatment.

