Regarding the subgroup analysis of diagnostic accuracy of [^18^F]PSMA‐1007‐PET/CT compared with Na[^18^F]F‐PET/CT, we assumed a prevalence of metastases of 30%, sensitivity and specificity of 0.38 and 0.91 for conventional imaging, respectively, and 0.85 and 0.98 for [^18^F]PSMA‐1007‐PET/CT, respectively. Then, a sample size of 128 patients is sufficient to indicate a superior sensitivity for [^18^F]PSMA‐1007‐PET/CT and a non‐inferior specificity for [^18^F]PSMA‐1007‐PET/CT with a non‐inferiority margin of 0.052 (power: 80%). This subgroup analysis will be made and published when the first 128 patients have been recruited in Group B.

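### In the accuracy subgroup, verification depends on one of the two scans compared, so absolute PSMA sensitivity, NPV and the specificity contrast are unreliable, in a direction that Table 3 leaves open

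*Protocol article*

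**What the plan says.** All references are to the protocol article.

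- **Study design:** "A subgroup of patients in Group B will have a blinded" NaF-PET with low-dose CT, for comparative accuracy. Under Diagnostic accuracy and stage migration, this scan is combined with the contrast-enhanced CT from the PSMA-PET/CT and goes to a team conference held only for research. The treatment decided clinically rests on the PSMA-PET/CT.
- **Reference standard:** typical lesions, especially in nodes and bones, are accepted as metastases without further examination. Beyond that: "Further imaging will be used as reference standard to confirm or exclude metastatic disease when clinically indicated". Also: "Biopsies are not performed solely as a part of the study".
- **Clinical management:** "If in doubt of metastases, further imaging or biopsy will be performed if possible and relevant".
- **Table 3** lists when a metastasis is deemed present; no row says when it is deemed absent. The node and liver rows name PSMA uptake. The bone row refers to marked uptake without naming a tracer.
- **Statistical analysis plan and sample size determination:** sensitivity, specificity and predictive values of both scans are judged against Table 3. The subgroup analysis is due once the first 128 Group B patients are recruited.
- **Appendix C** lists the endpoint as accuracy for bone metastases; the section on diagnostic accuracy also covers nodes and soft tissue.

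**The concern.** A PSMA or CT finding reaches the clinical team and can lead to imaging or biopsy, which then becomes the reference. A finding on the blinded NaF-PET alone cannot. A man negative on both scans is worked up only if something clinical calls for it. Whether a patient's true status is established therefore depends on one of the two tests under comparison.

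What happens to a NaF-only bone lesion then turns on how the bone row is read. If NaF uptake counts, the lesion makes the man reference-positive without work-up, whether or not it is a metastasis. If it does not count, the lesion tends to be scored as a NaF false positive, even when it is a metastasis that PSMA missed. Absolute PSMA sensitivity, its NPV and the specificity contrast all depend on that choice, and more patients do not reduce the error. Because the analysis is tied to recruitment, later follow-up cannot be relied on to correct it.

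**Working it through.** **Inputs** (sample size section): "we assumed a prevalence of metastases of 30"%; "sensitivity and specificity of 0.38 and 0.91 for conventional imaging"; "0.85 and 0.98 for [^18^F]PSMA‐1007‐PET/CT, respectively"; non-inferiority margin for specificity 0.052; "a sample size of 128 patients is sufficient to indicate a superior sensitivity". The plan gives no joint distribution of the two scans; conditional independence given true status is my assumption.

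**The plan's own figure.** With both specificities at 0.98, one-sided 5% and 80% power, the non-diseased needed are (1.645 + 0.842)² × 2 × 0.98 × 0.02 / 0.052² = 89.6, and 89.6 / 0.70 = 128.0. The stated 128 reproduces on these settings and is not in dispute.

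**Expected counts in 128 men** (38.4 with metastases, 89.6 without). NaF here stands for conventional imaging, to which the plan's 0.38 and 0.91 refer.

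| | Metastases | None |
|---|---|---|
| Both positive | 38.4×0.85×0.38 = 12.4 | 89.6×0.02×0.09 = 0.2 |
| PSMA only | 38.4×0.85×0.62 = 20.2 | 89.6×0.02×0.91 = 1.6 |
| NaF only | 38.4×0.15×0.38 = 2.2 | 89.6×0.98×0.09 = 7.9 |
| Neither | 38.4×0.15×0.62 = 3.6 | 89.6×0.98×0.91 = 79.9 |

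PSMA misses 2.2 + 3.6 = 5.8 men. About 10 men are positive on NaF only.

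**Three scenarios, as proportions of all men.**

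1. *All PSMA-negative men deemed disease-free.* Reference-positive 0.30×0.85 = 0.255. PSMA sensitivity 0.255/0.255 = 1.00; NaF 0.0969/0.255 = 0.38. NaF specificity 1 − (0.0171 + 0.063)/0.745 = 0.892; PSMA 1 − 0.014/0.745 = 0.981.
2. *Only metastases missed by both scans hidden.* Reference-positive 0.255 + 0.0171 = 0.2721. PSMA 0.255/0.2721 = 0.937; NaF 0.114/0.2721 = 0.419. Specificities 1 − 0.014/0.7279 = 0.981 and 1 − 0.063/0.7279 = 0.913.
3. *Every man positive on either scan deemed metastatic.* Reference-positive 0.2721 + 0.0757 = 0.3478. PSMA 0.269/0.3478 = 0.773; NaF 0.177/0.3478 = 0.509. No positive man is reference-negative, so both specificities read 1.00.

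| | Truth | 1 | 2 | 3 |
|---|---|---|---|---|
| PSMA sensitivity | 0.85 | 1.00 | 0.94 | 0.77 |
| NaF sensitivity | 0.38 | 0.38 | 0.42 | 0.51 |
| Difference | 0.47 | 0.62 | 0.52 | 0.26 |
| Sensitivity ratio | 2.24 | 2.63 | 2.24 | 1.52 |
| Specificity, PSMA minus NaF | 0.07 | 0.089 | 0.067 | 0 |
| PSMA NPV | 0.94 | 1.00 | 0.98 | 0.89 |

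NPV divides by the PSMA-negative share, 0.686 + 0.045 = 0.731: truth 0.686/0.731; scenario 2 (0.731 − 0.0171)/0.731; scenario 3 (0.731 − 0.0788)/0.731, where 0.0788 = 0.0171 + 0.0617 is the NaF-only share.

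In scenario 1 the specificity contrast moves by 0.019, over a third of the 0.052 margin. In scenario 2 the sensitivity ratio is unchanged: hiding metastases missed by both scans does not bias relative sensitivity.

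**Does superior sensitivity survive?** The difference favours PSMA throughout. In scenario 3, expected discordant reference-positives are 20.2 + 1.6 = 21.9 (before rounding of the parts) against 2.2 + 7.9 = 10.1, a McNemar z of (21.9 − 10.1)/√32.0 ≈ 2.1. That is close to 1.96, but only if every false NaF-only finding counts as a metastasis.

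**These are scenarios, not limits.** If NaF-only findings all count as true while PSMA positives are verified correctly, PSMA sensitivity is 0.255/(0.255 + 0.0788) = 0.764. The specificity contrast becomes 0.979 − 0.998 = −0.019, from false-positive shares 0.014/0.666 and 0.00126/0.666.

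**The case against.** Work-up is not the main reference. Typical nodes and bones are accepted from scan appearance, so blinding matters only for the remainder. The contrast-enhanced CT is unblinded, so conventional node and soft-tissue findings do reach the clinical team; the 10 or so NaF-only men in the table therefore overstate those cut off. Blinding NaF keeps Group B management PSMA-based, and avoiding study-only biopsies is a deliberate limit. An explicit rule for absence of disease may stand in the full protocol. The endpoint is secondary, and PFS is unaffected.

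All of this stands, and it narrows the point to NaF-PET findings, chiefly in bone, and to metastases missed by both scans. It does not remove it: Appendix C names bone as the accuracy endpoint, and the bone row is the one whose tracer is unstated.

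A reader might infer more, namely that the design necessarily inflates PSMA sensitivity, towards 100%, and biases both planned claims in its favour. The documents do not support that. The value 1.00 requires that no PSMA-missed metastasis is ever identified. If the bone row includes NaF uptake, NaF false positives verify themselves and PSMA sensitivity can read below 0.85.

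**Conclusion.** The concern holds in a limited form. Following the article as written gives accuracy figures whose verification depends on one of the two tests compared. Against an assumed 0.85, apparent PSMA sensitivity could read from about 0.77 to 1.00; NPV and the specificity contrast move with it. Neither the direction nor the size can be settled from the documents, because both depend on the reading of the bone row and on how many missed metastases come to light clinically. The range rests on the plan's prevalence and accuracy inputs and on conditional independence. Superior sensitivity would probably survive. This is worth correcting before the accuracy results are read; it does not touch the primary endpoint or the subgroup size.

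**What to change.** For the accuracy analysis only, with no change to patient care:

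1. State which tracer's uptake counts in the bone row of Table 3, and apply the same rule to lesions positive on either scan.
2. Have existing readers judge the evidence already generated, masked to which scan was positive.
3. Report relative sensitivity and relative false-positive rate (PSMA to NaF) among men positive on either scan, alongside the planned measures. These need no verification of men negative on both scans. They still depend on the NaF-only lesions, hence the next item.
4. Report bounds with unverified NaF-only lesions counted as all true and as all false.
5. Label absolute sensitivity and NPV as conditional on incomplete verification.

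Cost: some reader and analysis time, and wider, less favourable accuracy statements. No added scans, biopsies or patients. Using follow-up evidence would delay the report beyond the planned time, and would only partly help: the Discussion says that men with residual disease or recurrence after NaF staging are currently referred to PSMA-PET/CT, so follow-up imaging is itself often PSMA-based. The report should say so.

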### Diagnostic accuracy and stage migration

3.1

The secondary endpoint of diagnostic accuracy and stage migration will be performed in a subgroup of patients within Group B where patients will act as their own controls. Hence, the comparison will be made for Na[^18^F]F‐PET/CT versus [^18^F]PSMA‐1007‐PET/CT for diagnosing bone, lymph node and soft tissue metastases. For this purpose, the CECT from the [^18^F]PSMA‐1007‐PET/CT will be used together with the blinded Na[^18^F]F‐PET scan, which will be performed with a ldCT for sparing radiation to participating patients. In the same subgroup, we will determine the rate of stage migration and change of treatment strategy. This will be performed in an MDT‐similar set‐up for research purposes only. In this MDT, clinical information about the patients and the blinded Na[^18^F]F‐PET/CT scans will be used to make a first decision on the treatment strategy, which will subsequently be compared with the clinically decided treatment strategy based on the [^18^F]PSMA‐1007‐PET/CT. Due to potential stage migration in the PSMA group, we expect a change of treatment strategy in a smaller group of patients.

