### Statistical analysis plan and sample size determination

3.2

Descriptive statistics will be done according to data type: mean ± standard deviation or median (range) for symmetrically and asymmetrically distributed continuous variables, respectively, as judged visually with histograms including approximating normal curves; and frequencies and percentages for categorical variables.

The analysis of time‐to‐event endpoints (PFS, overall survival) will comprise Cox proportional hazard regressions adjusted for group, risk status (high‐, intermediate‐ and low‐risk PCa) and centre. Graphical displays will comprise Kaplan–Meier plots including risk tables (i.e., patients at risk in each group) and the results of respective log‐rank tests. The analysis of QoL data will comprise the estimation of the group difference in a repeated measurement analysis. Descriptive analyses will be performed, and results presented by proportions. Continuous variables will be compared using a *t* test, and categorical variables using a chi‐squared test. Additionally, regression analysis will be used to identify associations within data. Accuracy assessments of Na[^18^F]F‐PET/CT and [^18^F]PSMA‐1007‐PET/CT will relate to sensitivity, specificity, positive and negative predictive values that will be judged upon the reference standard (Table 3). Exploratory, bivariate testing will consist of unpaired *t* tests, alternatively, Wilcoxon's rank sum test, on continuous variables and chi‐squared test, alternatively, Fisher's exact test, on categorical variables. The level of significance will be 5% (two‐sided). All analyses will be done with STATA/IC 17 (StataCorp, College Station, TX 77845, USA).

A total of 402 patients (201 in each arm) are sufficient to indicate a statistically significant difference in PFS with assumed hazard rates of 0.35 and 0.5 for [^18^F]PSMA‐1007‐PET/CT and conventional staging, respectively, implying a hazard ratio of 0.7. Estimates are based on a study duration of 4 years, consisting of 3 years of accrual time and a minimum follow‐up period of 1 year (two‐sample comparison of survivor functions; exponential test; power: 80%). Accounting for loss to follow‐up of 10%, a total of 448 patients (224 in each arm) will be included in the study.

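### Table 3 makes PSMA uptake part of the reference standard for lymph nodes and liver, so the within-patient accuracy comparison has either no common truth or a truth that contains the PSMA result

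*Protocol article*

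**What the plan says.** Table 3 in section 2.5 of the protocol article is the reference standard. Its lymph node row reads "Equal to or more than 8 mm, round and with no fat in the hilum, for PSMA‐PET with uptake of PSMA", and its liver row reads "Biopsy if possible and clinically relevant, for PSMA‐PET with uptake of PSMA". Other rows allow a metastasis to be established by pathology in any organ except the prostate, or by further supporting imaging. Both routes are selective. Section 2.5 says "Biopsies are not performed solely as a part of the study" and "Further imaging will be used as reference standard to confirm or exclude metastatic disease when clinically indicated".

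Section 3.1 places the accuracy comparison in "a subgroup of patients within Group B where patients will act as their own controls". It covers bone, lymph node and soft tissue metastases, and the CECT acquired with the PSMA scan serves both tests. Section 3.2 ties the accuracy measures of both scans to Table 3 (sensitivity, specificity, "positive and negative predictive values that will be judged upon the reference standard (Table 3"). It plans 128 men to show superior sensitivity and non-inferior specificity of PSMA, with separate publication once they are recruited.

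**The concern.** A within-patient comparison of two tests needs one disease status per man, set without favouring either test. The clause on PSMA uptake does not provide this, whichever way it is read.

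- **First reading: the clause depends on the scan being scored.** The row asks for size and shape when NaF/CECT is scored, and for size, shape and PSMA uptake when PSMA is scored. Two discordant scans of the same node can then both be counted correct.
- **Second reading: the clause applies to all men who had PSMA-PET.** The whole subgroup had that scan, so the status is common. It now includes the result of one of the two tests under evaluation.

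The estimates at stake are the sensitivity and specificity that the subgroup publication would report. PSMA could look better, or the comparator worse, because of the wording of the reference.

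**Working it through.** **Inputs** (section 3.2): 128 men; prevalence of metastases 30%; sensitivity and specificity 0.38 and 0.91 for conventional imaging, 0.85 and 0.98 for PSMA; non-inferiority margin 0.052; power 80%.

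**Step 1. The plan's own figure.** Non-inferiority of specificity, taking 0.98 for both tests and a one-sided 5% level:

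n = (1.645 + 0.842)² × 2 × 0.98 × 0.02 / 0.052² ≈ 89.6 men without metastases.

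89.6 / 0.70 ≈ 128.0, or 90 / 0.70 = 128.6 if rounded up first. The 128 is reproduced and is not in dispute.

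**Step 2. One man, two readings.** Take a man whose only finding is a node of 8 mm or more, round, without a fatty hilum and without PSMA uptake, and with no pathology or further imaging.

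| Reading of the clause | Status when NaF/CECT is scored | Status when PSMA is scored |
|---|---|---|
| Depends on the scan scored | metastatic; CECT true positive | not metastatic; PSMA true negative |
| All men who had PSMA-PET | not metastatic; CECT false positive | not metastatic; PSMA true negative |

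In neither row can PSMA be charged with a miss.

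**Step 3. Effect on PSMA sensitivity (both readings).** Metastatic men: 128 × 0.30 = 38.4. Found by PSMA: 0.85 × 38.4 = 32.64. Missed: 5.76. Let f be the share of misses known only as enlarged PSMA-negative nodes. The documents give no value for f, so the range is an assumption. These men leave the denominator:

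sensitivity = 32.64 / (38.4 − 5.76 f)

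- f = 0: 0.85
- f = 0.25: 32.64 / 36.96 = 0.88
- f = 0.50: 32.64 / 35.52 = 0.92
- f = 1: 32.64 / 32.64 = 1.00

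At f = 1 the prevalence in the PSMA analysis is 32.64 / 128 = 25.5%. On the first reading the NaF analysis of the same men still has 30%. PSMA specificity hardly moves (0.980 to 0.981).

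**Step 4. Effect on the comparator (second reading).** Men without metastases: 128 × 0.70 = 89.6; correctly negative on conventional imaging: 0.91 × 89.6 = 81.54. The reclassified men join the non-metastatic group as CECT positives:

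specificity = 81.54 / (89.6 + 5.76 f), which is 0.90, 0.88 and 0.86 for f = 0.25, 0.50 and 1.

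sensitivity = (14.59 − 5.76 f) / (38.4 − 5.76 f), which is 0.36, 0.33 and 0.27, against the planned 0.38 (0.38 × 38.4 = 14.59).

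**Step 5. Would deleting the clause be enough?** What remains is size and shape, which is nearly the CECT reading rule of section 2.4 (more than 8 mm there, 8 mm or more in Table 3). Suppose g benign enlarged PSMA-negative nodes, g = 4 or 8 (assumed; conventional imaging has 89.6 − 81.54 = 8.1 false positives in all), become metastatic for both scans:

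- PSMA sensitivity: 32.64 / (38.4 + g) = 0.77 or 0.70
- comparator sensitivity: (14.59 + g) / (38.4 + g) = 0.44 or 0.49
- comparator specificity: 81.54 / (89.6 − g) = 0.95 or 1.00

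Deletion alone would therefore replace a bias towards PSMA with a bias towards CECT.

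**The case against.** Table 3 serves the whole trial, including Group A, where no PSMA scan exists. The clause may simply mean men staged with PSMA-PET. A reader might infer that every enlarged PSMA-negative node has two contradictory statuses and that the paired table cannot be formed. The text does not establish that, because on this second meaning there is one status per man. This objection stands, but it leaves the reference containing the PSMA result.

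A reader might also infer that PSMA can never miss an enlarged node. That goes too far. Table 3 accepts pathology and further imaging, and section 2.6 sends doubtful cases for further imaging or biopsy where possible and relevant. A PSMA-negative node confirmed in that way is a PSMA miss. What remains is that these routes follow clinical need, so an unknown share of nodes is decided by the row alone.

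Nor do the documents support saying that a finding of superior sensitivity would be produced by the wording. The planned gap is 0.85 against 0.38, and with 38 metastatic men the power is about 99% (unpaired approximation) without any inflation. The bias does not all run towards PSMA either: the size rule is close to the CECT reading rule, and a PSMA-positive node under 8 mm fails the row.

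Finally, Appendix C lists only the accuracy of evaluating bone metastases for this comparison. Section 3.1 expressly adds lymph nodes and soft tissue, and the point applies under that section.

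**Conclusion.** The point holds as a defect in the reference standard for the accuracy subgroup. Under either meaning of the clause, a node decided by the size-and-uptake row alone is classified in a way that protects PSMA from a miss.

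The possible overstatement of PSMA sensitivity runs from nothing to 0.15 (0.85 to 1.00), depending entirely on the assumed share f. The upper end needs every PSMA miss to be an enlarged PSMA-negative node with no other confirmation, which is an extreme. The fall in comparator specificity applies to the second reading only and assumes that all these nodes are read as positive on CECT.

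No firm statement on the non-inferiority test is warranted. The second reading lowers comparator specificity and makes the test easier to pass. The first can raise comparator specificity, if benign enlarged nodes count as metastatic for NaF/CECT, and so make it harder. The issue is bias in a secondary endpoint. It should be settled before the subgroup results are published.

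**What to change.** For the accuracy analysis only, with no change to clinical staging or management:

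1. Assign each man one disease status (and each region one status, if regions are analysed), and score both scans against it.
2. Let pathology decide first, then further imaging and follow-up already collected. Either may confirm or exclude a metastasis.
3. Do not simply delete the PSMA clause, for the reason shown in step 5 of the working. Flag men whose status rests only on index-scan criteria, whether CECT size and shape or PSMA uptake, and report accuracy with and without them.
4. State whether the endpoint covers nodes and soft tissue as well as bone, so that section 3.1 and Appendix C agree.

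The cost is a wording change and some adjudication work on existing data, without extra scans, biopsies or patients. The estimates may become less favourable to PSMA, and those that leave out the flagged men will be less precise.

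### In the accuracy subgroup, Table 3 lets a scan's own bone uptake or typical pattern prove a metastasis, which biases bone specificity upward and makes the non-inferiority test too easy to pass

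*Protocol article*

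**What the plan says.** Section 3.2 of the protocol article ties sensitivity, specificity and both predictive values to section 2.5: they are measures "that will be judged upon the reference standard (Table 3"). Three rules there accept imaging appearance as sufficient:

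- **Bones (Table 3):** "Marked uptake of activity with or without malignant morphology in CT and not related to joint with degenerative changes or a fracture". Malignant morphology with uptake is the alternative route. The row names no tracer.
- **Typical presentation (text of 2.5):** "Metastatic disease will be deemed without further imaging or examinations if the presentation is considered of typical morphology and pattern for PCa". Nodes and bones are singled out.
- **Disseminated disease (Table 3):** with a typical pattern, "disseminated disease can be determined without further imaging or biopsy".

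Independent evidence is allowed but not systematic. "Biopsies are not performed solely as a part of the study", and "Further imaging will be used as reference standard to confirm or exclude metastatic disease when clinically indicated". Nodes follow a size-and-shape rule, "Equal to or more than 8 mm, round and with no fat in the hilum", with PSMA uptake added for PSMA-PET.

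Section 3.1 makes the comparison within patients for bone, node and soft-tissue disease; Appendix C lists bone accuracy only. Section 3.2 plans superior sensitivity and non-inferior specificity with 128 patients and margin 0.052, reported once the first 128 Group B patients are recruited.

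**The concern.** A reference standard should rest on something other than the test being judged. For bone it largely does not. Under Appendix B, a PSMA lesion with high uptake and no anatomical correlate (score 4) is already suggestive of malignancy, and with a correlate (score 5) it is definite. Table 3's bone row accepts nearly the same finding as proof. This is incorporation bias: a confident false positive in bone enters the table as a true positive and leaves the specificity denominator.

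The independent checks do not reliably catch it. Work-up follows clinical doubt (section 2.6), so a confident wrong read is the least likely to be checked. Because the report is tied to recruitment of 128 patients, the article secures no follow-up in which an error could show itself.

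At stake is a formal claim with its own sample size and publication: that PSMA-PET/CT finds more disease without an unacceptable loss of specificity. The second half of that claim is the part affected.

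**Working it through.** **Inputs (section 3.2):** N = 128; prevalence 0.30; sensitivity/specificity 0.38/0.91 for conventional imaging and 0.85/0.98 for PSMA; margin 0.052; power 80%. The general significance level is 5% two-sided; none is given for the non-inferiority test.

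**1. The plan's 128.** Metastasis-free patients needed = (z_alpha + z_power)² × [p1(1−p1) + p2(1−p2)] / (p2 − p1 + margin)².

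- Both specificities 0.98, one-sided 0.05: 6.183 × 0.0392 / 0.052² = 89.6, so 90. Divided by 0.70 this is 129, which matches 128 within rounding.
- Stated 0.91 and 0.98, one-sided 0.025: 7.849 × 0.1015 / 0.122² = 53.5, so 54, or 78 patients.

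The stated figure thus appears to rest on equal specificities and one-sided 5%. That is a separate matter; here it only supports using one-sided 0.05 below.

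**2. Effect of self-verification.** Let f be the share of PSMA false-positive reads that Table 3 turns into reference-positives. These reads leave the denominator, so

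apparent specificity = S / [S + (1 − S)(1 − f)].

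Put true PSMA specificity exactly at the margin, S = 0.91 − 0.052 = 0.858, where a valid test should pass about 5% of the time. For example, at f = 0.5: 0.858 / (0.858 + 0.142 × 0.5) = 0.858 / 0.929 = 0.92.

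The pass rate was simulated with 20,000 trials of 128 patients, a paired Wald test at one-sided 0.05 and conditionally independent reads. Two cases bracket the article's silence on whether the blinded NaF scan informs the reference.

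| f | Apparent PSMA specificity | False pass, both scans verify themselves at rate f | False pass, only PSMA feeds the reference |
|---|---|---|---|
| 0 | 0.858 | 6% | 6% |
| 0.5 | 0.923 | 17% | 47% |
| 0.8 | 0.968 | 50% | 92% |
| 1 | 1.000 | 100% | 100% |

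When both scans verify themselves, apparent NaF specificity also rises (0.91 / 0.955 = 0.953 at f = 0.5), so the inflation is smaller. A one-sided 0.025 test would lower the intermediate rates; at f = 1 it would still always pass.

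**3. The limiting case.** If uptake decided every positive, again with independent reads:

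- P(PSMA+) = 0.3 × 0.85 + 0.7 × 0.02 = 0.269
- P(NaF+) = 0.3 × 0.38 + 0.7 × 0.09 = 0.177
- P(both+) = 0.3 × 0.85 × 0.38 + 0.7 × 0.02 × 0.09 = 0.098
- P(either+) = 0.269 + 0.177 − 0.098 = 0.348

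With either scan as truth, both specificities read 1.00 and sensitivities read 0.269/0.348 = 0.77 (PSMA) and 0.177/0.348 = 0.51 (NaF). With PSMA as truth, PSMA reads 1.00/1.00, NaF sensitivity 0.098/0.269 = 0.36 and NaF specificity 0.652/0.731 = 0.89. This is a ceiling, not a forecast.

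**4. Nodes.** Section 2.4 reads CT nodes as possibly malignant above 8 mm, round and without hilar fat, nearly the node reference rule itself. A PSMA-positive node under 8 mm fails that rule and can count as a PSMA false positive, although the typical-presentation sentence also covers nodes. In nodes the bias can therefore run against PSMA.

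**The case against.** A reader might infer that bone false positives are almost impossible and that non-inferiority is met by construction. The article does not support that:

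- The bone row asks for marked uptake and excludes uptake explained by degenerative joints or fracture.
- The text of 2.5 requires typical morphology as well as pattern.
- Score 3 lesions are queried for work-up. Section 2.6 provides further imaging or biopsy in doubtful cases, and 2.5 lets further imaging exclude metastasis.

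False positives in bone can therefore still be recorded.

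The numbers also have limits. The planning inputs are for metastases at all sites, while the clearest defect is in bone. Conditional independence is doubtful because both reads share one contrast-enhanced CT. The documents give no value for f.

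A reader might also infer that one lesion must have two reference statuses, since some rows add PSMA uptake only for PSMA-PET. That wording can equally mean wherever a PSMA scan exists, which is every subgroup patient. Nor does anything say that the blinded NaF scan feeds the reference.

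Finally, the endpoint is secondary. The PFS comparison, its sample size and the interim look at stage distribution do not use accuracy estimates.

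These points narrow the concern and rule out the limiting case as an estimate. They do not remove it: exclusion depends on doubt, and confident positive reads raise none.

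**Conclusion.** The concern holds in limited form. For lesions read confidently, the reference standard repeats the index read, so bone specificity is biased upward for whichever scan informs the reference. The specificity test is close to empty for the bone-only endpoint of Appendix C if most positives are self-verified. For the all-site analysis of section 3.1 it is distorted rather than empty, with the node rule able to pull the other way.

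With true PSMA specificity at the margin, the false-pass rate is about 6% without self-verification, 17–47% at one half and 50–92% at 80%. These figures assume conditionally independent reads, all-site inputs and a one-sided 5% test. They show how sensitive the claim is to an unreported share; they do not predict the trial's result.

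**What to change.** For the accuracy endpoint only, leaving clinical staging as it is, amend section 2.5, Table 3 and the accuracy paragraph of section 3.2:

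1. Assign one reference status per lesion or patient, applied to both scans, and state which scans inform it, including whether the blinded NaF scan does.
2. Where available, base it on pathology, later imaging obtained clinically, and the PSA and clinical course already followed for PFS.
3. Flag lesions whose only evidence is index-scan uptake or pattern as self-verified, and report accuracy separately for independently verified and self-verified lesions.
4. Give sensitivity and specificity with all self-verified lesions taken as true, then all as false. Claim non-inferior specificity only if it holds across both.

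Unverified lesions should not simply be dropped from specificity. What remained would be selected by clinical doubt, and unverified false positives would still be missing from the denominator.

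This requires no scan or biopsy beyond clinical care. The cost is wider intervals, a weaker claim and possibly a later accuracy report.
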